#### Peak power output (PPO)

PPO is assessed as the peak wattage achieved during CPET and represents the maximum mechanical power produced by lower extremity musculature. PPO is considered a measure of the physical functional reserve. In pwMS, lower PPO is correlated with higher energetic costs of walking [32].

#### Walking capacity

Walking capacity is tested using the six-minute walk test (6-MWT). Participants are asked to walk back and forth on a 30-meter hallway for the duration of six minutes, performing 180° turns around cones at each end [33]. According to the modified 6-MWT script, participants are instructed to walk at maximum speed. Breaks or any kind of encouragement are not permitted. Participants are allowed to use an assistive walking device, if necessary to ensure safe ambulation. 6-MWT performance is defined as the total distance in meters covered within six minutes. The modified 6-MWT has excellent inter-rater and intra-rater reliability, and correlates with fatigue, self-reported physical functionality, and perceived ambulation impairment in pwMS [34].

#### Cognitive performance

Cognitive performance is tested using the validated German modification of the Brief International Cognitive Assessment for Multiple Sclerosis (BICAMS-M). Similar to the original BICAMS, this modified version comprises three subtests evaluating information processing speed, verbal memory, and visuospatial memory [35]. The Symbol Digit Modalities Test (SDMT) evaluates information processing speed. The participant is displayed a code of nine abstract symbols, paired with nine digits. Underneath the code, incomplete rows are presented that only contain the abstract symbols in a pseudo-random order. The participant is asked to verbally match as many digits as possible to the corresponding abstract symbol within 90 seconds. SDMT performance is indicated by the number of correct matches, written down by the outcome assessor. Instead of the California Verbal Learning Test, the German language Verbal Learning and Memory Test (VLMT) was adopted, as norm data are based on a larger validation cohort. The VLMT is used to assess verbal memory. Participants are read aloud a 15-word list five times. After each repetition, participants are asked to immediately recall as many words as possible. VLMT performance is indicated by the summed number of correct words across the five trials. The Brief Visuospatial Memory Test-Revised (BVMT-R) is performed to assess visuospatial memory. The participant is asked to memorize six abstract geometric figures, presented on a 2 × 3 array for ten seconds. After these ten seconds, the array is removed. The participant is asked to copy the six figures on a blank form. The procedure is repeated three times. For each trial, the outcome assessor rates the shape, size, and location of the figures on a 0-2 scale. Higher ratings indicate better performance. Overall BVMT-R performance is indicated by the summed number of ratings across the three trials [36, 37]. Parallel versions of the VLMT and the BVMT-R are used at T_4_. For the SDMT, no parallel version is used as learning effects are considered to be minor [37, 38]. The validated BICAMS-M allows to detect cognitive impairment in MS and is a reliable instrument to monitor cognitive performance over time [37].

#### Health-related quality of life

HRQoL is assessed using the German version of the Multiple Sclerosis Impact Scale (MSIS-29). The MSIS-29 comprises two subscales, addressing the physical impact (20 items), and psychological impact (9 items) of MS. Items address upper and lower limb functionality, ambulation, incontinence, sleep, emotional well-being as well as disease-related limitations in daily living, and societal participation. Each item is ranked on a 5-point Likert scale. Higher scores indicate a greater impact of MS and lower HRQoL. To calculate subscale scores, individual scores are summed, averaged, and transformed to a 0-100 scale [39, 40]. The German version additionally allows to calculate a total MSIS-29 score that is the arithmetic mean of both subscale scores [40, 41]. The MSIS-29 is a responsive measure in MS rehabilitation, and has been used in pwPPMS [42]. The German version of the MSIS-29 has been proven to be valid and reliable [40, 41].

#### Fatigue

MS-related fatigue is assessed with the German version of the Fatigue Scale for Motor and Cognitive Functions (FSMC). The FSMC is a multidimensional 20-item composite scale that comprises a 10-item motor and a 10-item cognitive subscale. Items are rated on a 5-point Likert scale. Higher values indicate greater total, motor, or cognitive fatigue, respectively. Cut-off values allow to identify substantial fatigue (i.e., FSMC composite score ≥ 43), and to classify fatigue severity as mild, moderate, or severe. The FSMC composite scale as well as both subscales have been proven to be reliable, and are sensitive and specific for detecting MS-related fatigue [43].

#### Anxiety and depressive symptoms

Anxiety and depressive symptoms are assessed with the validated German version of the Hospital Anxiety and Depression Scale (HADS). The HADS is used in non-psychiatric populations with medical ailments, and includes 14 items that allow evaluation of anxiety (7 items) and depressive symptoms (7 items). Items are scored on a 4-point Likert scale. According to the original HADS manuscript, separate sum scoring is performed for the items on anxiety and depressive symptoms. Higher values indicate greater severity of anxiety or depressive symptoms. Subscale score ranges are used to distinguish between non-cases (0-7 points), doubtful cases (possible anxiety/depression, 8-10 points), and cases (probable anxiety/depression, 11-21 points) [44, 45]. A HADS total score of ≥ 13 points is considered to indicate overall psychological distress [46, 47]. For the German population, normative values are available [46]. In pwMS, the HADS is a sensitive and specific self-report measure that supports the detection of major depression, and/or generalized anxiety disorder [48].

#### Blood-derived biomarkers

Blood sampling is performed in a fasted state. Samples are obtained from the antecubital vein in supine position. To evaluate the chronic effects of HIIT and MCT on blood-derived biomarkers, resting blood samples are taken between 8:00 and 9:00 AM after ten minutes of supine rest (T_1_, T_4_). To evaluate acute effects on blood-derived biomarkers, blood samples are taken immediately after (T_2_) and two hours after (T_3_) the first HIIT or MCT session. Per sampling time point, two whole blood collection tubes (BD Vacutainer^®^, BD CPT™, 4ml), prefilled with lymphocyte separation medium, and one serum tube (tube vacutainer SSTII serum yel, 6ml) are taken.

Blood samples are analysed regarding the acute and chronic effects of HIIT and MCT on KP modulation, and surrogate markers of neurodegeneration (i.e., sNfL, glial fibrillary acidic protein (GFAP)).

Whole blood samples are centrifuged at 3500 g for 20 minutes, separating peripheral blood mononuclear cells (PBMCs) and plasma. PBMCs are resuspended in plasma, purged into centrifugation tubes, diluted with an equal amount of phosphate-buffered saline, and centrifuged at 2400 g for 10 minutes. The supernatant is discarded. PBMCs are resuspended in cell culture freezing medium, and aliquoted. Aliquots are frozen at -80 °C until analysis. mRNA of PBMCs is isolated using a commercial column-based isolation kit. cDNA synthesis is performed. Based on mRNA and cDNA, gene expression of KP-relevant genes is determined. As such, expression levels of indoleamine 2,3-dioxygenase-1, kynurenine aminotransferase 1–4, kynurenine-3-monooxygenase, aryl hydrocarbon receptor, CYP1A1, interleukin-4-induced-1, and SLC7A5 are determined using real-time quantitative polymerase chain reaction (qPCR), run on a qTower³ G touch (Analytik Jena GmbH, Jena, Germany). Blood serum is centrifuged at 2500 g for 20 minutes, is aliquoted, and frozen at -80 °C until analysis. Targeted metabolomics (liquid chromatography tandem mass spectrometry (LC-MS/MS)) is performed at BEVITAL AS, Bergen, Norway, to determine serum concentrations of tryptophan, KP downstream metabolites (e.g., kynurenine, kynurenic acid, quinolinic acid), and B vitamers. Systemic concentrations of sNfL and GFAP are assessed using a single molecule array (SiMoA HD-1 device, Quanterix, USA) at the University Medical Center of the Johannes Gutenberg University, Mainz, Germany, according to the manufacturer’s instructions.

Sequences and time frames of assessment procedures are depicted in the SPIRIT 2013 diagram (Fig. 2).

**Fig. 2 Fig2:**
[figure not shown]
SPIRIT 2013 diagram Abbreviations: HIIT = high-intensity interval training; MCT = moderate-intensity continuous training; MoCA = Montreal Cognitive Assessment; CPET = cardiopulmonary exercise testing; PPO = peak power output in watts during CPET; BICAMS-M = German modification of the Brief International Cognitive Assessment for Multiple Sclerosis; 6-MWT = six-minute walk test; MSIS-29 = Multiple Sclerosis Impact Scale; FSMC = Fatigue Scale for Motor and Cognitive Functions; HADS = Hospital Anxiety and Depression Scale. T_− 1_= day of admission; T_0_ = day of study entry (baseline assessment prior group allocation); T_1_ = immediately before the first exercise session; T_2_ = immediately after the first exercise session; T_3_ = two hours after the first exercise session; T_4_ = at discharge after three weeks, at least 48 h after the last exercise session

#### Compliance

Drop-out and session attendance as well as reasons for study withdrawal and incomplete session attendance are captured in total, and separately for HIIT and MCT. Participants who drop out continue standard rehabilitative care at the Valens rehabilitation clinic, as far as medical conditions allow. Participants are not replaced. Collected data are stored upon the termination of data analysis. None of the assessments planned at later stages are conducted. The attendance rate is calculated as the number of completed sessions by the number of prescribed sessions. Protocol adherence to the prescribed duration and intensity is derived from HR recordings of HIIT and MCT sessions upon completion of data collection. Reasons for session abortion or protocol deviations, including but not limited to dose modifications and adverse events, are questioned, and documented in a case report form. Severe adverse events (e.g., cardiovascular decompensation) are directly reported to the local Ethics committee. Overall compliance is assessed by comparing prescribed Units of Exercise to performed Units of Exercise per group, combining measures of adherence (intensity (%HR_peak_), session duration (minutes)), and attendance (total number of sessions, i.e., number of sessions per week x number of weeks) [25]. Compliance will be given as percentage of prescribed Units of Exercise.

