### Participants

Inclusion criteria for CYPRO comprise adult age (≥ 18 years), definite PPMS diagnosis, Expanded Disability Status Scale (EDSS) score  ≤ 6.0, and signed consent [21–23]. Exclusion criteria concern severe lower extremity spasticity or concomitant disease states (i.e., orthopaedic, cardiovascular, metabolic, psychiatric, other neurological, serious medical conditions) that would impair the ability to participate. Pregnant or breastfeeding women or those intending to become pregnant are excluded. Further, pwPPMS are prohibited to participate, if they regularly perform HIIT (i.e., ≥ 2 times per week), if non-compliance is suspected, if they are not able to follow study procedures (e.g., due to insufficient German literacy), or in case of a recent treatment change (e.g., change in disease-modifying treatment (≤ 6 weeks), stem cell treatment (≤ 6 months)). PwPPMS are excluded from further participation in case of severe adverse events (e.g., cardiovascular decompensation) during cardiopulmonary exercise testing (CPET) at baseline, sudden severe disease progression, or falling sick (e.g., due to bacterial or viral infections) during the participation in CYPRO.

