#### Safety considerations

Exercise is safe in pwMS and not associated with a higher risk of adverse events compared to exercise in healthy individuals [26]. Similarly, HIIT on bicycle ergometers is well-tolerated and holds a low risk of adverse events in pwMS [27]. As in healthy individuals, transient knee and/or leg pain, or muscle soreness may occur in response to HIIT and MCT sessions. Between HIIT and MCT sessions, participants receive at least 48 hours of rest to ensure adequate recovery. Supervising therapists are instructed to prevent, monitor, and document the occurrence of adverse events, if any. To prevent injuries or falls, participants may be assisted in getting on and off the bicycle ergometer, if necessary. HR monitoring, rating of perceived exertion (RPE, Borg Category Ratio-10-point (Borg CR-10) scale), and observation of vegetative signs serve to minimize any risk of overexertion [28]. Study personnel may need to withdraw participants in case of repeatedly reported adverse events (e.g., leg pain), the occurrence of severe adverse events (e.g., cardiovascular decompensation), or other medical reasons (e.g., infections). In those cases, participants are forwarded to a physician for medical clearance. With the signature of the consent form prior to participation, participants confirm that they are informed about potential exercise-related risks and the right to refrain from participation in CYPRO at any time.

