### Outcomes

V̇O_2peak_, PPO, walking capacity, cognitive performance, HRQoL, fatigue, and anxiety and depressive symptoms are assessed by allocation-blinded outcome assessors at study entry (baseline, T_0_) and discharge after three weeks (T_4_), at least 48 hours after the last HIIT or MCT session. Venous blood samples are taken before (T_1_), immediately after (T_2_), and two hours after (T_3_) the first HIIT or MCT session, and at T_4_.

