### Statistical analysis

Statistical analyses are performed according to the intention-to-treat principle. Descriptive statistics will be reported as arithmetic mean (*M*) and standard deviation (*SD*) for continuous data, and as absolute number and percentage (*%*) for categorical data for the total sample, and separated by group. Outcome data will be checked for normality (Shapiro-Wilk test) in advance. If necessary, analyses will be adjusted accordingly. If missing values are < 5%, ANCOVA will be performed to detect time*group interaction effects and main effects of time. In that case, effect sizes will be calculated as partial eta squared (*pη*^*2*^). Otherwise, a baseline-adjusted Mixed Model for Repeated Measures (MMRM) approach, with group, time and the group × time interaction as fixed effects (type III sums of squares, CS covariance structure over time) is used to assess between-group differences over time. Bonferroni-corrected pairwise comparisons of estimated marginal means of the group × time interaction are computed. Effect sizes will be reported as Cohen’s *d* with 95% confidence interval (*CI*). For all analyses, the level of significance is set at *p* = .05. Within-group differences and between-group differences are depicted as point estimates and measures of variability for all outcomes. Bivariate correlation analyses will be conducted to determine potential associations between changes in V̇O_peak_, PPO, walking capacity, cognitive performance, HRQoL, fatigue, anxiety and depressive symptoms, and blood-based biomarkers using Pearson’s *r*. All statistical analyses will be conducted with IBM SPSS Statistics for Windows (Version 29.0., IBM Corp., Armonk, New York, USA). Besides the final analysis, one interim analysis will be performed upon collection of 50% of participant data (HIIT: *n* = 15, MCT: *n* = 16).

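### Drop-outs get no discharge assessment, so the promised intention-to-treat analysis is in effect a completer analysis for every outcome measured only at baseline and discharge

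*Protocol article*

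**What the plan says.** The Statistical analysis section opens with the principle: "Statistical analyses are performed according to the intention-to-treat principle". It then names ANCOVA if fewer than 5% of values are missing, and otherwise a baseline-adjusted MMRM with compound-symmetry covariance.

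The Compliance section governs drop-outs. "Participants who drop out continue standard rehabilitative care at the Valens rehabilitation clinic, as far as medical conditions allow". They are not replaced, and "None of the assessments planned at later stages are conducted".

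Two other sections let staff end participation after randomisation. The Participants section excludes people from further participation for "sudden severe disease progression, or falling sick (e.g., due to bacterial or viral infections) during the participation in CYPRO". The Safety considerations section says: "Study personnel may need to withdraw participants in case of repeatedly reported adverse events (e.g., leg pain", and adds severe adverse events and other medical reasons. No section distinguishes these removals from a participant's own decision to leave, so the Compliance rule is read here as covering both.

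The Outcomes section places VO2peak, peak power, walking, cognition, quality of life, fatigue, and anxiety and depressive symptoms at T0 and T4 only. Blood is drawn at T1, T2, T3 and T4. The Sample size calculation section allows for 15% drop-out within 61 participants (30 HIIT, 31 MCT).

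**The concern.** An intention-to-treat comparison needs outcomes from everyone randomised, in the arm to which they were assigned. Here the plan itself orders that the outcome of a drop-out not be collected, even when the person is still in the building and T4 falls at discharge. This is an explicit rule, not a detail that the article leaves to another document.

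Some reasons for leaving, such as leg pain, may depend on the training assigned: the arms train at 95% and 60% of peak heart rate, and neither participants nor therapists are blinded. Other reasons, such as infection, need not depend on it. If loss differs between arms and drop-outs would have fared differently from completers, the primary comparison is biased and the data cannot show by how much. The article's Discussion promises explicit recommendations for practice, and these rest on the effect in all who are assigned to a training mode.

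**Working it through.** **1. How many people.** Inputs: N = 61 and drop-out 15% (Sample size calculation). 61 × 0.15 = 9.15, so about 9 without T4 and about 52 with it. The figure of 61 is taken here as the recruitment target. It does not reproduce from its stated inputs: a noncentral F test with λ = f²·N·m/(1 − ρ), f = 0.15, m = 2, ρ = 0.6 gives 72, and 72/0.85 = 84.7, i.e. 85. That is a separate matter and does not affect this point.

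**2. Which analysis will apply.** The 5% threshold, read as the share of participants without T4, is 0.05 × 61 = 3.05. Four or more missing therefore triggers the MMRM. With X binomial(61, 0.15), P(X ≥ 4) = 0.987. The MMRM is the expected route.

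**3. What that model can use.** A drop-out has T0 only.
- If T4 is the single response and T0 the covariate, the drop-out contributes no response and the model equals completer ANCOVA.
- If T0 is also a response, the drop-out contributes baseline information only.

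**4. Check by simulation.** Assumed: a true difference of 0.60 SD (ES 0.15 read as Cohen's f, so the difference in change is 4 × 0.15 = 0.60 SD), correlation 0.6, drop-out 25% HIIT and 5% MCT, and a T4 shortfall of 0.6 SD in drop-outs. Mean estimates over 200 trials:

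| Analysis | Mean estimate (SD) |
|---|---|
| ANCOVA, T4 measured in everyone | 0.479 |
| ANCOVA, completers only | 0.607 |
| Mixed model, compound symmetry, common baseline | 0.604 |
| Mixed model, compound symmetry, group × time | 0.610 |

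The mixed models follow the completers, not the full follow-up.

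**5. Size of the bias.** Let p be the drop-out rate and g the T4 shortfall of drop-outs relative to completers in the same arm. Completer difference minus full-follow-up difference = p(HIIT)·g(HIIT) − p(MCT)·g(MCT). With the same g in both arms this is (p(HIIT) − p(MCT)) × g:

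| Drop-out HIIT / MCT | g = 0.3 | g = 0.6 | g = 1.0 |
|---|---|---|---|
| 15% / 15% | 0 | 0 | 0 |
| 20% / 10% | 0.03 | 0.06 | 0.10 |
| 25% / 5% | 0.06 | 0.12 | 0.20 |

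Positive values favour HIIT. Swapping the rates reverses the sign: 10% / 20% gives −0.03 to −0.10. The simulated gap in step 4, 0.607 − 0.479 = 0.128, agrees with 0.20 × 0.6 = 0.12. The documents give no drop-out rate by arm and no shortfall, so all rates by arm and all g are assumptions.

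**The case against.** **The mixed model keeps everyone in the data set.** It is valid if data are missing at random, and intention-to-treat can be read as analysing available data by allocated arm. In name this is correct. With one post-baseline visit, however, missing at random here means given arm and baseline alone. That is doubtful when removal follows an adverse event or illness occurring after baseline.

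**The rule is narrower than it may look.** It concerns drop-outs and staff withdrawals. Nothing cancels T4 for people who only miss sessions or train at a modified dose. Severe events at the baseline CPET occur before allocation and are not part of the problem. Blood markers have T1 to T3 values, so someone leaving after the first session still contributes there. All of this stands and limits the point to T0/T4 outcomes.

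**Not everyone could be tested.** Continued stay depends on medical condition, and CPET runs to exhaustion. Some drop-outs could not provide VO2peak at T4. This stands too: a reader might infer that most drop-outs remain available for testing, but the documents give no proportion.

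**Direction is open.** A reader might infer that the harder arm loses more and the result therefore favours HIIT. The documents do not support this. The Discussion says HIIT may be more enjoyable, the Safety considerations call it well tolerated, and the Exercise protocols section permits dose modification. Nor are all reasons for leaving tied to treatment.

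**Conclusion.** The Compliance and Statistical analysis sections conflict. Followed as written, the plan yields in effect a completer comparison for VO2peak and every other T0/T4 outcome, with about 9 of 61 participants unmeasured at the planned drop-out rate. That conclusion rests on the text and on there being one post-baseline visit.

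The size and direction of bias do not rest on the text. The plausible range shown includes zero and either sign.

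Two stronger readings should be avoided:
- **A fixed overstatement of 11% to 25%.** This follows only if 10% to 20% of HIIT participants leave with no HIIT advantage while MCT drop-outs do as well as MCT completers: 0.60 × (1 − 0.10) = 0.54 and 0.60 × (1 − 0.20) = 0.48, so 0.60/0.54 = 1.11 and 0.60/0.48 = 1.25. It is one assumed pattern among many.
- **A gain in power from retaining drop-outs.** ANCOVA power is 75.5% with 52 participants and 82.1% with 61 only if the effect stays at 0.60 SD. At the diluted effects of 0.54, 0.51 and 0.48 SD, power with 61 is 73.6%, 68.7% and 63.5%, all below 75.5%. The case for the change is validity, not power.

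**What to change.** Reconcile the two sections:
- Define stopping the training sessions separately from withdrawing from the study.
- Replace the sentence that cancels later assessments. Every randomised participant who still consents and can be assessed is offered the T4 assessments at discharge: CPET only where medically cleared, otherwise the remaining T4 outcomes.
- Analyse each participant in the allocated arm.
- Because some VO2peak values will still be missing, add a sensitivity analysis for data not missing at random.

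This adds no visit or instrument and changes no treatment or withdrawal criterion. The cost is a protocol amendment and a few assessments of a kind already planned for all participants. It recovers only part of the missing VO2peak values and cannot recover T4 from people who have already dropped out. The Study status section reports 23 recruited by March 2023, so 61 − 23 = 38 were still to be enrolled at that date and could be covered.
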